## Abstract

**Background:**

In in vitro fertilization (IVF) and intracytoplasmatic sperm injection (ICSI) treatment a large drop is present between embryo transfer and occurrence of pregnancy. The implantation rate per embryo transferred is only 30%. Studies have shown that minor intrauterine abnormalities can be found in 11–45% of infertile women with a normal transvaginal sonography or hysterosalpingography. Two randomised controlled trials have indicated that detection and treatment of these abnormalities by office hysteroscopy after two failed IVF cycles leads to a 9–13% increase in pregnancy rate. Therefore, screening of all infertile women for intracavitary pathology prior to the start of IVF/ICSI is increasingly advocated. In absence of a scientific basis for such a policy, this study will assess the effects and costs of screening for and treatment of unsuspected intrauterine abnormalities by routine office hysteroscopy, with or without saline infusion sonography (SIS), prior to a first IVF/ICSI cycle.

**Methods/design:**

Multicenter randomised controlled trial in asymptomatic subfertile women, indicated for a first IVF/ICSI treatment cycle, with normal findings at transvaginal sonography. Women with recurrent miscarriages, prior hysteroscopy treatment and intermenstrual blood loss will not be included. Participants will be randomised for a routine fertility work-up with additional (SIS and) hysteroscopy with on-the-spot-treatment of predefined intrauterine abnormalities versus the regular fertility work-up without additional diagnostic tests. The primary study outcome is the cumulative ongoing pregnancy rate resulting in live birth achieved within 18 months of IVF/ICSI treatment after randomisation. Secondary study outcome parameters are the cumulative implantation rate; cumulative miscarriage rate; patient preference and patient tolerance of a SIS and hysteroscopy procedure. All data will be analysed according to the intention-to-treat principle, using univariate and multivariate logistic regression and cox regression. Cost-effectiveness analysis will be performed to evaluate the costs of the additional tests as routine procedure. In total 700 patients will be included in this study.

**Discussion:**

The results of this study will help to clarify the significance of hysteroscopy prior to IVF treatment.

**Trial registration:**

NCT01242852

## Background

Despite the numerous advances in the field of in vitro fertilisation (IVF) and intracytoplasmic sperm injection (ICSI), the maximum implantation rate per embryo transferred is still approximately 30%. Even if both ovum pick-up and fertilization occur successfully in the process of IVF, there is a large unexplained gap between successful embryo transfer and occurrence of pregnancy. Implantation failure presents a major clinical challenge and is a cause of considerable stress to patients and clinicians in assisted reproductive technology (ART). Besides the psychological and physical burden of each IVF treatment cycle, it also adds to the considerable costs associated with fertility treatment [1]. If progress is to be made in improving implantation rates, a greater understanding of the factors which determine successful implantation is required.

Implantation failure could be due to the embryo, uterine environment or a combination of both. Even minor uterine cavity abnormalities, such as endometrial polyps, small submucous myomas, adhesions, and septa are considered to have a negative impact on the chance to conceive through IVF [2]. The prevalence of unsuspected intrauterine abnormalities, diagnosed by hysteroscopy prior to IVF, has been reported to be 11–45% [3-13]. Therefore, it has been proposed that these abnormalities should be diagnosed and treated in order to optimize the condition of the uterine environment and thus the outcome of IVF treatment. However, this recommendation is not based on high quality evidence [3,5,7-10]. In addition, the benefits of hysteroscopy in patients who will undergo a first IVF/ICSI treatment have not yet been investigated.

At present, the basic work-up for evaluation of the uterine cavity prior to IVF consists of transvaginal ultrasound, possibly followed by saline infusion sonography (SIS), hysterosalpingography (HSG) or hysteroscopy. The accuracy of HSG in assessment of the uterine cavity integrity in subfertile patients has been reported to be rather disappointing [14,15]. SIS is increasingly considered to be useful in diagnosing intrauterine abnormalities. It is an inexpensive, non-invasive diagnostic test, and has been proven to be very accurate [16,17]. Yet hysteroscopy is still considered to be the gold standard. It has become easy to perform in an outpatient clinic without anesthesia. Moreover, hysteroscopy enables diagnosis and treatment of intrauterine pathology in the same setting.

The NVOG (Dutch society of Obstetrics and Gynaecology) as well as the ESHRE (European Society for Human Reproduction and Embryology) and RCOG (Royal College of Obstetricians and Gynaecologists) do not recommend SIS nor hysteroscopy as initial investigation prior to starting IVF [18-20]. It has been argued that the significance of treating unsuspected intrauterine abnormalities has not yet been proven.

So far, none of the guidelines considered the most recent literature on this topic. In a retrospective cohort analysis, Gera et al. compared the pregnancy rate after operative hysteroscopy of patients with intrauterine abnormalities at SIS to the pregnancy rate of patients with a normal uterine cavity. A 31.6% increase in pregnancy rate was observed after treatment of detected abnormalities [21]. Furthermore, two randomized trials reported exceptional improvements in pregnancy rates after office hysteroscopy and instant treatment of detected pathology in patients after two failed IVF attempts. Intervention resulted in a 9–13% increase in clinical pregnancy rate in the subsequent IVF cycle [7,9]. These results endorsed the findings of other, previously published prospective studies [3,5]. Despite some methodological weaknesses in the study design, the results of these studies indicate a trend towards a beneficial effect of screening hysteroscopy on IVF outcome. This finding, combined with the observed high prevalence of intrauterine abnormalities, has led to a general debate on the beneficial effect of pre-IVF work-up of the uterine cavity.

The current study aims to clarify the additive value of routine SIS and/or hysteroscopy prior to IVF/ICSI . Also, patient preferences and the cost-effectiveness of these tests as routine procedures for assessment of the uterine cavity prior to starting IVF will be assessed.

## Methods

### Study design

The inSIGHT trial is a multicenter randomised controlled trail (RCT). A total of twenty-five academic and non-academic centers in the Netherlands will participate. An economic analysis is incorporated to assess the cost-effectiveness of the investigated tests as routine procedures prior to IVF. Inclusion was started in May 2011.

This study will be conducted according to the principles of the Declaration of Helsinki and in accordance with the Medical Research Involving Human Subjects Act (WMO). The study protocol has been approved by the medical ethical review committee of the University Medical Center Utrecht (MEC 10–272) and by the board of directors of all participating centers. The protocol is registered at clinicaltrial.gov NCT01242852.

### Recruitment, consent and randomisation

Women with an indication for a first IVF/ICSI treatment cycle will be informed about this trial by their attending physician. They will also receive written patient information. One to two weeks after the first visit, the coordinating investigator will counsel the woman. If a woman agrees to participate in the study, informed consent will be obtained and randomisation will be performed for one of two strategies: routine infertility work-up followed by immediate IVF (control arm) or the routine work-up with additional diagnostic tests ((SIS and) hysteroscopy) with on-the-spot treatment of intrauterine pathology followed by IVF (intervention arm) (Figure 1). Randomisation will be performed centrally by a web-based randomisation program and will be stratified according to recruiting center.

**Figure 1 F1:**
[figure not shown]
Flowchart inSIGHT study.

### Study population

All women with primary or secondary infertility scheduled for a first IVF/ICSI treatment cycle at one of the participating hospitals who have a normal transvaginal ultrasound are considered to be eligible for inclusion. A normal transvaginal ultrasound is defined as no visible intracavitary pathology (e.g. submucous myomas, polyps or septa) and will be performed in the follicular phase of the menstrual cycle. Intramural myomas without impression or deformation of the uterine cavity are incorporated in the definition of a normal ultrasound. Exclusion criteria are recurrent miscarriage, defined as 2 or more miscarriages prior to the 20^th^ week of gestation, prior hysteroscopy treatment and intermenstrual blood loss.

### Interventions

#### Intervention arm

All women in the intervention group will undergo routine fertility work-up with additional tests. In five of the twenty-five research hospitals the additional tests consist of SIS and hysteroscopy. In all the other participating hospitals the additional test will consist of solely a hysteroscopy.

SIS will be performed prior to the hysteroscopy on CD 3–9. A speculum will be inserted vaginally and up to 20 ml of sterile saline solution will be infused into the uterine cavity through a catheter to distend the endometrial cavity. A transvaginal transducer will be used to scan the uterine cavity. The findings at SIS will be recorded in a standardised manner on the case record form (CRF).

The hysteroscopy examination will be scheduled in the early-mid follicular phase of a menstrual cycle (day 3–12). The hysteroscopy examinator will be blinded for SIS outcomes. A vaginoscopic approach will be used without anesthesia in an outpatient setting. Only if the examination cannot be accomplished due to patient intolerance, the possibility of a paracervical block will be offered. Hysteroscopy will be performed using a 5-mm outer-diameter continuous flow hysteroscope with a 5 French working channel and a 30 direction of view. The uterine cavity will be distended by saline infusion. The endocervical canal, uterine cavity, tubal orifices and endometrium will be inspected methodically and findings recorded on a standardized form. Intrauterine abnormalities will be defined as endometrial polyps, septate uterus, adhesions and chronic or acute endometritis. A sample of the endometrium will be obtained for histological examination by a gentle biopsy with a ‘pipelle’ biopsy canulla or grasping forceps. Therapeutic hysteroscopy will be performed in the same hysteroscopy session if any of the predefined intrauterine abnormalities is detected. It is left to the judgement of the operator physician to decide to perform a septum resection in a subsequent session with laparoscopic observation. After the hysteroscopy, the resected tissue will be examined histologically by a pathologist for the presence of chronic or acute endometritis.

To assess patient tolerance of SIS and a diagnostic/therapeutic hysteroscopy, all patients will be asked to complete a standardized questionnaire, containing questions about the level of tolerance and acceptability of both procedures.

#### Control arm

All women allocated to the control group will be scheduled for IVF or ICSI and undergo standard treatment, without SIS or hysteroscopy.

#### Fertility treatment

All randomised women, be it allocated to intervention or control arm, will undergo IVF. In the intervention group IVF treatment will be started within 3 months after hysteroscopy. Rec-FSH or HMG combined with a GnRH agonist protocol (Leuprolide or Triptorelin 100 microgram) or a GnRH antagonist protocol (Ganirelix/Cetrorelix 0.25 mg/d) will be used. Final oocyte maturation will be achieved by the administration of HCG when 3 or more follicles of more than 16 mm are present. Oocyte retrieval will be carried out 36 hours after HCG administration. Luteal phase supplementation consists of 600 mg natural micronised progesterone in three separate dosages (Urogestan®/Progestan® 100 mg 3x2/day) starting in the evening after oocyte retrieval and continued until 18 days after ovum pick-up.

### Withdrawal of individual patients

Subjects can abandon the study at any time for any reason if they wish to do so without any consequences. The investigator can decide to withdraw a subject from the study for urgent medical reasons.

## Outcome measures

The primary endpoint of this study will be the cumulative ongoing pregnancy rate resulting in live birth achieved within 18 months of IVF/ICSI treatment after randomisation.

Secondary study parameters/endpoints will be the cumulative implantation and miscarriage rate within 18 months of IVF/ICSI treatment after randomisation, cost calculations of SIS, hysteroscopy procedures and the IVF treatment, patient preference and tolerance of SIS and diagnostic/therapeutic hysteroscopy procedure and presence of unexpected intracavitary abnormalities (e.g. endometrial polyps, septate uterus, adhesions and endometritis) prior to IVF/ICSI.

To investigate the cost-effectiveness of SIS and hysteroscopy as routine procedures prior to IVF treatment, a cost analysis will be performed. The economic evaluation is performed from a societal perspective. Differentiation will be made between direct medical costs (all health care sector costs), direct non-medical costs (costs outside the health care sector that are affected by health status or health care) and indirect costs of the fertility treatment (costs of sick leave due to fertility treatment). For medical costs, the process of care is divided into three cost stages (cost of SIS, cost of hysteroscopy, cost of IVF treatment), which can reoccur in case of repeat treatment cycles. Costs will be computed from the period of inclusion to the end of follow-up (18 months).

Health care utilisation in the fertility treatment consists of visits to hospital, ultrasound, gonadotrophins, oocyte retrieval, lab work of IVF (including various laboratory tests) and hospital care. Volumes of health care resources use will be measured prospectively alongside the clinical study. At this stage, direct non-medical and indirect costs may be generated if women are absent from paid work, either for visiting the fertility clinic during IVF treatment, or for sick leave associated with physical or psychological side-effects of this treatment. The Health and Labor Questionnaire [22] will be used to document absence from paid work.

## Statistical analysis

### Sample size calculation

Based on the literature, the increase in ongoing pregnancy in women with recurrent IVF failure after treatment of predefined abnormalities of the uterine cavity is found to be 9–32% in the subsequent IVF/ICSI cycles [5,7,9].

In a group of women indicated for a first IVF/ICSI treatment cycle, the difference in cumulative live birth rate after 18 months of IVF/ICSI treatment is estimated to be 10% between the patients with and without hysteroscopy (40% versus 30%). The number of patients needed to have 80% power (with alpha = 0.05) to detect such a difference is 350 per study arm.

To be able to answer the question on the benefit of using SIS as a pre-selection tool the following sample size calculation for patients needing to have both SIS and hysteroscopy was made. From previous literature, the prevalence of unsuspected intrauterine abnormalities is considered to be 12% and the sensitivity of SIS compared to hysteroscopy to be 95% [11]. SIS and hysteroscopy need to be performed in 160 women to achieve a 95% confidence interval of 10% (85–100%). This means that a total of 320 women need to be randomised in the five hospitals in this study that perform SIS.

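### The 85–100% interval for SIS sensitivity rests on a normal approximation that fails with about 19 affected women; a valid interval is about 74–100%

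*Protocol article*

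**What the plan says.** The last paragraph of the Sample size calculation section in the protocol article sizes the SIS sub-question separately from the primary comparison. Its purpose is given as "To be able to answer the question on the benefit of using SIS as a pre-selection tool".

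The planning values are that "the prevalence of unsuspected intrauterine abnormalities is considered to be 12" per cent and "the sensitivity of SIS compared to hysteroscopy to be 95" per cent. From these it concludes: "SIS and hysteroscopy need to be performed in 160 women to achieve a 95% confidence interval of 10% (85–100" per cent). Because only the intervention arm has SIS, this becomes "a total of 320 women need to be randomised in the five hospitals in this study that perform SIS".

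The article does not name the interval method and does not give the expected number of women with an abnormality.

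The Economic analysis section then evaluates a strategy in which hysteroscopy follows only an abnormal SIS. It plans sensitivity analyses over assumptions and parameter estimates.

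**The concern.** The 160 women are not the denominator for sensitivity. Only those in whom hysteroscopy shows an abnormality count, and at 12% prevalence they are few. An interval from 85% to exactly 100%, described as 10% around a value of 95%, suggests a symmetric formula that overshot 100% and was cut back.

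In the SIS-first strategy, an abnormality that SIS misses is not followed by hysteroscopy. The lower end of the interval therefore says how many abnormalities that strategy might overlook. The article tells the reader that up to about 15% missed is compatible with the expected result. If the honest lower limit is nearer 74%, the figure is about 26%, and the information on SIS as a pre-selection tool is much weaker than stated.

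**Working it through.** **Inputs, all from the Sample size calculation section:** prevalence 0.12; sensitivity 0.95; 160 women with both tests; 95% confidence; target 85–100%. The 10% can only be the half-width around 95%: read as the total width (half-width 5%), the same formula needs about 73 affected women, or about 608 with both tests.

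**1. Reproducing the 160.** Wald formula for one proportion:

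- affected women needed = 1.96² × 0.95 × 0.05 / 0.10² = 18.25, rounded up to 19
- women needed = 19 / 0.12 = 158.3, so 159, in line with the stated 160

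Forward check: 160 × 0.12 = 19.2 affected; half-width = 1.96 × √(0.95 × 0.05 / 19.2) = 0.0975; interval 85.3% to 104.7%, cut at 100%. The article's figure is thus reproduced.

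**2. Whether the approximation is usable.** Expected misses = 19.2 × 0.05 = 0.96. With 19 affected women and a true sensitivity of 95%:

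- All 19 are detected with probability 0.95¹⁹ = 0.377. The Wald interval then has zero width (100–100%) and excludes the true value.
- Summed over all possible results, the Wald interval contains 95% with probability 0.62, not 0.95.

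**3. Intervals suited to this size (95%, two-sided).**

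| Method | 18 of 19 detected | Lower limit, 19 of 19 detected |
|---|---|---|
| Clopper-Pearson | 74.0–99.9% | 82.4% |
| Wilson | 75.4–99.1% | 83.2% |
| Agresti-Coull | 73.5–100% | 80.2% |
| Jeffreys | 77.9–99.4% | 87.8% |

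At the expected result of 18 of 19, all four lower limits fall 7 to 11.5 points below 85%.

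**4. Chance that the lower limit reaches 85%.** The number affected is taken as binomial (160, 0.12), with 5th to 95th percentile 13–26, and the number detected as binomial with probability 0.95:

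- Clopper-Pearson 5.8%
- Wilson 8.2%
- Jeffreys 29%

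With no misses, 85% is cleared from 22 affected women (Wilson, 85.1%) or 23 (Clopper-Pearson, 85.2%).

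**5. Size that would give 85% at an observed 95%.** Treating the count as continuous, about 49 affected women (Wilson) or 51 (Clopper-Pearson), that is about 408 or 426 women with both tests. With whole-number counts at or just below 95% detected, 55 (52 detected, Wilson) or 56 (53 detected, Clopper-Pearson), that is 459 or 467 women. The range is roughly 410–470, about 2.6 to 2.9 times the planned 160.

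**The case against.** **The sum is not wrong.** This is correct: step 1 reproduces it from the article's own inputs. The fault lies in the choice of approximation.

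**85% is not out of reach.** A reader might infer from the 19-of-19 result that the design cannot show a lower limit of 85%. The figures do not support that. Jeffreys gives 87.8% at 19 of 19, and 22 or 23 affected women with no misses clear 85% by Wilson or Clopper-Pearson, a count well within chance variation. Unlikely is the supportable word.

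**Prevalence may be higher.** The Abstract and Background cite 11–45%, and 12% is near the bottom. At 30%, 160 women would include 48 with an abnormality, and 46 of 48 detected gives a Clopper-Pearson lower limit of 85.7%. This is fair as a qualification, but the stated interval is tied to the 12% that the article itself adopts.

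**No pass mark, and no stated Wald analysis.** The article gives 85–100% as a target precision, not as a threshold that SIS must meet, so a rule for accepting or rejecting SIS on its lower limit should not be read into it. The Statistic analysis section names no interval for sensitivity, and that choice may sit in an analysis plan that is not shown. It does not follow that a Wald interval will be reported. The point concerns the precision that this article states.

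**It is secondary.** SIS accuracy is not named among the endpoints in Outcome measures, and the Economic analysis section already plans to vary its parameters. That limits the severity but does not make the stated interval valid.

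**Conclusion.** The stated precision for SIS sensitivity is wrong as written. On the article's own 12% prevalence and 95% sensitivity, 160 women yield about 19 with an abnormality. The expected 95% interval is then about 74–100%, with a lower limit some 10 to 11 points below the stated 85% (Clopper-Pearson or Wilson; about 7 points below with Jeffreys). The chance of a lower limit of at least 85% is about 6–8% with Clopper-Pearson or Wilson.

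These results assume that the planning prevalence and sensitivity hold and that all 160 women have both tests. A higher prevalence would narrow the interval. The finding is a should-fix: it affects a secondary diagnostic question and has no bearing on the comparison of live birth with 350 women per arm.

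**What to change.** Keep 160 women with both tests and 320 randomised in the SIS hospitals. Then:

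- Replace the precision statement with wording such as: *about 19 women with an abnormality are expected among 160; an observed sensitivity near 95% then gives a 95% confidence interval of about 74–100%.*
- Report sensitivity with a Wilson or Clopper-Pearson interval rather than a Wald interval, in the analysis plan if that is where the method is set.
- Carry the wider range for sensitivity into the planned cost-effectiveness sensitivity analysis of the SIS-first strategy.

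This needs no extra patients and no change to trial conduct. The cost is a less favourable, but accurate, statement of what the SIS sub-question can show. If the sponsor wants a lower limit of 85% at an observed 95%, about 410–470 women with both tests would be needed at 12% prevalence, or about 820–940 randomised 1:1 in the SIS hospitals. That exceeds the whole planned trial of 700.

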### Economic analysis

For each strategy, live birth rate as well as the average costs per patient will be estimated and used to calculate cost-effectiveness ratios. Incremental cost-effectiveness ratios will be estimated for two strategies of additional diagnostic/therapeutic procedures: SIS followed by hysteroscopy if SIS is abnormal or no SIS but direct hysteroscopy. These two strategies will be compared to no additional investigations (routine fertility investigation followed directly by IVF/ICSI). Robustness of the results (costs and health outcomes) for various assumptions and parameters estimates will be explored in sensitivity analyses and visualized in ICER-graphs and cost-effectiveness acceptability curves.

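### The economic analysis compares SIS triage and direct hysteroscopy each with no testing and states no comparison between the two, so the stated ratios cannot settle the pre-selection question

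*Protocol article*

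**What the plan says.** The Economic analysis section of the protocol article plans ICERs for two active strategies: "SIS followed by hysteroscopy if SIS is abnormal or no SIS but direct hysteroscopy". It then fixes the comparator: "These two strategies will be compared to no additional investigations (routine fertility investigation followed directly by IVF/ICSI". Neither that section nor any other part of the article sets the two active strategies against each other.

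The same section plans the quantities behind the ratios: "For each strategy, live birth rate as well as the average costs per patient will be estimated and used to calculate cost-effectiveness ratios". It also plans sensitivity analyses, with results "visualized in ICER-graphs and cost-effectiveness acceptability curves". It does not say whether one set of curves will hold all three strategies.

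The Sample size calculation section makes triage a question of the trial and sizes a subgroup for it: "To be able to answer the question on the benefit of using SIS as a pre-selection tool". Its inputs are a prevalence of 12% and "the sensitivity of SIS compared to hysteroscopy to be 95" per cent. On cost, the Background says of SIS only this: "It is an inexpensive, non-invasive diagnostic test, and has been proven to be very accurate".

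**The concern.** No extra test, SIS triage and direct hysteroscopy are mutually exclusive. An ICER guides a choice among such options when each is compared with the next less costly option that is neither dominated nor extendedly dominated. If triage is cheaper than direct hysteroscopy and finds most of the same lesions, the comparator for direct hysteroscopy is triage. Measured against no testing, direct hysteroscopy is credited with births that triage would already deliver.

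Both strategies could then pass a willingness-to-pay limit against no testing. A reader of those two ratios would not learn what each extra birth costs when a clinic moves from triage to hysteroscopy for all.

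**Working it through.** **Plan figures checked first.** The article contains no ICER to reproduce. Two of its figures bear on the check.
- SIS precision: 160 × 0.12 = 19.2 affected women. The half-width is 1.96 × √(0.95 × 0.05 / 19.2) = 0.097, which gives about 85% to 100% after truncation. This matches the stated interval, so 85% is a fair lower value for sensitivity.
- Effect size: "estimated to be 10% between the patients with and without hysteroscopy (40% versus 30" per cent. With a two-sided 5% test and 80% power this needs 356 per arm (pooled variance). The stated 350 gives 79.3% power, which is close enough.

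**Inputs.** From the article: prevalence 0.12; sensitivity Se = 0.95, with 0.85 and 1.00 as the ends of its interval. Assumed, because the article gives neither: SIS cost *s* = 0.20 to 0.50, with the cost of one hysteroscopy set to 1; specificity Sp = 90% to 100%. Also assumed: all gained births come through detected and treated lesions, and only test costs differ.

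**Formulas.** *D* is the gain in live birth rate from direct hysteroscopy.
- SIS-positive rate: q = 0.12·Se + 0.88·(1 − Sp)
- Direct versus none: 1 / D
- Triage versus none: (s + q) / (Se·D)
- Direct versus triage: (1 − s − q) / ((1 − Se)·D)
- Multiple, direct versus triage over direct versus none: (1 − s − q) / (1 − Se)

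*D* cancels from the multiple while only test costs are counted.

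**Results.**

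| Case | s | Sp | q (Se 0.95) | Triage cost s + q | Multiple, Se 0.95 | Multiple, Se 0.85 |
|---|---|---|---|---|---|---|
| High | 0.20 | 100% | 0.114 | 0.314 | 0.686/0.05 = 13.7 | 0.698/0.15 = 4.7 |
| Mid | 0.30 | 95% | 0.158 | 0.458 | 0.542/0.05 = 10.8 | 0.554/0.15 = 3.7 |
| Low | 0.50 | 90% | 0.202 | 0.702 | 0.298/0.05 = 6.0 | 0.310/0.15 = 2.1 |

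At Se = 1.00, triage yields the same births at a cost of 0.320, 0.464 or 0.708 in the three cases. All are below 1, so direct hysteroscopy is dominated.

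**Worked example in ratio form.** Take D = 0.10, s = 0.25 and Sp = 90%. Triage costs 0.25 + 0.202 = 0.452.
- Triage versus none: 0.452/0.095 = 4.8 hysteroscopy costs per extra live birth
- Direct versus none: 1/0.10 = 10.0
- Direct versus triage: 0.548/0.005 = 109.6

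At any limit between 10 and about 110, direct hysteroscopy passes against no testing and fails against triage.

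**Where the multiple shrinks or reverses.**
- *Treatment cost.* If treating an affected woman costs 2, the mid case at Se = 0.95 becomes (0.542 + 0.012)/(0.05 × 1.24) = 8.9.
- *Benefit from hysteroscopy itself.* If half the gain comes this way, triage keeps 0.5 × 0.95 + 0.5·q of it. Mid case: 0.475 + 0.079 = 0.554, so the multiple is 0.542/0.446 = 1.2. Low case: 0.475 + 0.101 = 0.576, so the multiple is 0.298/0.424 = 0.70, and triage is extendedly dominated.
- *Dear SIS.* At s = 0.75 and Se = 0.95, the multiple is 2.7 at Sp = 100% and 0.96 at Sp = 90%. At Sp = 80% triage is dominated, since it costs 1.04 and yields fewer births. The multiple equals 1 at s = 0.95 − q, which is 0.84, 0.75 and 0.66 for Sp = 100%, 90% and 80%.

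**The case against.** **The plan does not exclude the direct comparison.** A reader might infer that it does. The article names one comparator and is silent on any other, and a condensed article can leave dominance rules and curve layout to a fuller document. This limits the point but does not remove it: the article states a comparator rule, and that rule alone does not serve the question.

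**Nothing is lost.** Mean cost and live birth rate are planned for every strategy, so the missing ratio follows by subtraction. This stands. The flaw lies in the stated comparison, not in the data.

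**No testing is a natural baseline.** Under Interventions, SIS is done within the intervention arm at five hospitals, and those women all have hysteroscopy as well. There is no SIS arm, nobody is managed by triage, and that strategy must be modelled. The only randomised contrast is hysteroscopy against none. This is a good reason to keep those comparisons, but not to omit the third.

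**Average ratios.** A reader might infer that the per-strategy cost-effectiveness ratios will rank the options. The article does not say so, and its next sentence turns to incremental ratios.

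**The multiple is fragile.** This stands too. A 10-point gain at 12% prevalence needs 0.10/0.12, about 83 points, in affected women if all benefit runs through lesions, which is hardly plausible. The plan also looks for endometritis by biopsy, and the article does not say that SIS detects it. Under Outcome measures the costing is societal over 18 months and includes IVF and sick leave. If births change those costs, the multiple depends on the effect size after all.

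**Conclusion.** The point holds in this form: the two stated ICERs, taken alone, cannot show whether direct hysteroscopy is worth its cost over SIS triage, although the trial sets SIS pre-selection as a question. The size is unknown. Under the cost and specificity ranges assumed above, with all benefit through detected lesions, the direct-versus-triage ICER is about 6 to 14 times the direct-versus-none ICER at 95% sensitivity and about 2 to 4 times in the low and mid cases at 85%. At 100% sensitivity direct hysteroscopy is dominated. The multiple can fall to about 1 or below if part of the benefit comes from hysteroscopy itself, or if SIS costs about 75% of a hysteroscopy or more, with the exact turning point set by specificity.

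A stronger reading would be that the plan will lead to the wrong strategy being called cost-effective. The documents do not support that. They state no decision rule, no costs and no specificity, and the quantities needed to see the problem are planned. The matter concerns a secondary economic analysis and leaves the randomised comparison and the primary endpoint untouched. The change should still be made, because it is specific and nearly free.

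**What to change.** Add a full incremental analysis of the three strategies to the Economic analysis section:
- Rank the strategies by mean cost and remove dominated and extendedly dominated options.
- Report each remaining option's ICER against the next less costly one, and state explicitly that this includes direct hysteroscopy against modelled SIS triage.
- Draw the acceptability curves for all three strategies jointly.
- Vary SIS sensitivity, specificity and cost in the sensitivity analyses.
- Keep the comparisons with no testing as secondary results.

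This costs a few sentences and slightly more analysis on data already planned. The small downside is that the ratio for direct hysteroscopy may look less favourable.
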